[71]. BI provides a quantification of the extent to which examiners disagree on the proportions of positive (or negative) indications. BI also ranges between 0 and 1, and is high when the difference between the discordant indications is high, chance agreement is consequently low, and kappa is inflated accordingly (bias)
[71]. P_pos_ and P_neg_ are the proportions of agreement on positive and negative indications, respectively, relative to the total number of positive and negative indications, respectively, from both therapists. Overall kappa (95% CI) will be calculated as a generalized chance-corrected reliability across all pairs of therapists. See Additional file
1 for formulas.

In addition, for each pair of therapists, separate 2×2 tables will be presented for judgements about the indication for PIVM assessment and for judgements about mobility, end-feel, and pain provocation obtained from PIVM assessment (four tables in total). Observed agreement, prevalence of positive decisions, PI, BI, p_pos_, p_neg_, and overall kappa (95% CI) will also be calculated. Analyses will be conducted using DAG_Stat
[72].

Kappa (95% CI) is interpreted in accordance with value labels as assigned by Landis & Koch
[73]: <0.00: poor, 0.00-0.20: slight, 0.21-0.40: fair, 0.41-0.60: moderate, 0.61-0.80: substantial, 0.81-1.00: almost perfect. We arbitrarily assume a lower bound of the 95% CI around overall kappa of 0.60 to indicate acceptable reliability.

Univariable logistic regression analysis will be performed to explore which demographic, professional, and clinical factors contributed to the reliability of therapists’ decision-making. Firstly, patients’ demographic and clinical factors at baseline will concern their gender, age, type of complaints, duration of complaints (less or more than three months), radiation, traumatic origin, comorbidity, pain intensity, and disability. Such factors are associated with variation in diagnostic accuracy
[74], but evidence in the context of reliability is lacking. Secondly, therapists’ professional factors will include their clinical experience and weekly amount of work related to spinal disorders. Weekly amount of work related to spinal disorders was positively associated with perceived importance and confidence related to the use and interpretation of PIVM assessment

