[20] and may, therefore, contribute to variation in diagnostic decision-making. In addition, other clinical factors will be explored involving PIVM assessment (indicated or not, and judgements on mobility, resistance, and pain provocation), the diagnostic conclusion (specific or non-specific neck or low-back pain), therapists’ level of certainty of their decision about the treatment indication, and the concordance between examination objectives and the use of PIVM assessment. Factors will be entered in the model as single covariates with the concordant decisions, either positive or negative, as the dependent variable. Concordant decisions will be coded as 1 while the discordant decisions will be coded 0. Therapists’ experience and work related to spinal disorders will be entered as mean scores from each pair. A p-value <0.05 indicates a statistically significant association between a factor and a concordant decision about whether or not SMT is indicated.

With a sample size of 165, a two-sided 95% CI around kappa would extend ±0.109 from the observed value of kappa, assuming a true value of kappa of 0.70, and a prevalence of positive decisions of 50%. Consequently, each pair of examiners will be asked to include 12 patients. Multiple imputation will be used to handle records with data points missing at random. If, for any reason, data on the primary outcome measure are not available or obtainable from one or both therapists, all data from this patient will be excluded from the analysis and the pair of therapists will be asked to include a new patient. Analyses will be conducted using IBM SPSS Statistics for Windows version 22.

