Awaiting evidence from the further validation of prediction rules and other classification systems, our study could offer an initial step toward a faster and easier development of an alternative approach to the identification of those patients with spinal disorders that may show a better response to SMT based on a multivariable decision process. A satisfactory level of reliability is a prerequisite for incorporating such decision-making into the design of randomised clinical trials for establishing treatment effects of SMT and thereby validating the approach. When reliability (lower bound of 95% CI around kappa) exceeds 0.60 and with BI, arbitrarily, <0.10, patients with neck or low-back pain with a positive indication can be randomised to receive, for instance, either manual mobilisations or manipulations, or both, within a multimodal treatment on the one hand or multimodal treatment without mobilisations or manipulations on the other (Figure 
1A). Should reliability be below this cut-off but with p_pos_ (or p_neg_), arbitrarily, >60%, this strategy can still be used by randomising only those patients of which the indication was agreed upon by two manual therapists (Figure 
1B). P_pos_ and p_neg_ here indicate the absolute specific agreement on positive or negative indications, respectively, between therapists
[25].

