**Figure 1 F1:**
[figure not shown]
**A. Design of an RCT including patients positively indicated for SMT when lower bound of 95% CI around kappa >0.60 and BI <0.10. B**. Design of an RCT including only patients positively indicated for SMT by two examiners when kappa <0.60 but p_pos_ (or p_neg_) >60%.

With respect to our second research objective, it is important to note that empirical evidence for sources of bias and variation in reliability studies is lacking contrary to studies of diagnostic accuracy
[74,93-95]. Variation arises from differences between studies, for example, in terms of demographic and disease features of study participants, characteristics of examiners, setting, or test protocol. As such, it does not lead to biased estimates of reliability, but it can limit the applicability of study results
[94]. Knowledge of factors that explain variation in reliability may inform ways to improve reliability. For instance, examiner training and choosing a group of more heterogeneous study participants have been mentioned as improvement strategies, but both have their limitations and lack supporting evidence
[24]. Systematic reviews may reveal subgroups of participants, examiners, or tests that consistently show higher or lower reliability. In systematic reviews, between-study comparisons are conducted to search for these subgroups as sources of variation. However, these comparisons are less valid as they are hampered by the often strong clinical and methodological heterogeneity between studies
[96]. In addition, the identification of these sources of variation becomes even more troublesome when reliability is consistently low (or high) across studies. Within-study comparisons are the preferred method to explore variation in reliability. To date, very few studies have been undertaken in the field of manual therapy with this aim and method. Cook et al.
[97] investigated factors related to the large variability of forces used during passive accessory intervertebral movements and they found that examiners’ age, gender, experience, background and education, and frequency of use did not contribute to this variation. We present simple logistic regression analysis of concordant decisions as a flexible method that can easily be incorporated in any reliability study to explore and explain variation in reliability from a large number of demographic, professional, and clinical factors.

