[103-113]. Within the large variation in choices of treatment options by therapists, mobilisations and manipulations were only rarely among the most preferred options and their frequency of use ranged from 16% to 83% and from 2% to 37%, respectively. These figures were not substantially different for specific subgroups of manual therapists who reported remarkably low frequencies of use of manipulations in the cervical region
[36,114-116]. As we will consider reliability of indicating either mobilisations or manipulations, or both, we assume a 50% prevalence of positive indications. Choosing a higher or lower prevalence would have resulted in a larger required sample
[117].

In our sample of manual therapists and patients, we cannot rule out the possibility of a substantially higher (or lower) prevalence of positive indications for SMT. Because of such a skewed distribution of decisions, a distorted interpretation of kappa could then occur. Recently, kappa, as a relative measure of reliability, has been criticised because it can only provide information about the ability to distinguish between patients on a sample level
[25]. The authors suggest using the specific agreement parameters (p_pos_ and p_neg_) as absolute measures to quantify observer variation regarding a certain diagnosis or decision on an individual patient level
[25]. No single omnibus index, however, can be satisfactory for all purpose and situations
[69,70]. Therefore, we will calculate all recommended parameters from the 2×2 tables to allow full interpretation of reliability and agreement as related to the prevalence of concordant and discordant indications. We will not, however, correct kappa for prevalence effects and bias, for instance by calculating prevalence-adjusted bias-adjusted kappa, because this would generate values of reliability that no longer relate to the original situation
[117,118].

We will select pairs of manual therapists as examiners that share a common educational background. With this background from the largest institute for manual therapy education in the Netherlands, they likely form a representative sample from the Dutch population of manual therapists registered with the Dutch Association for Manual Therapy or the Royal Dutch Society for Physical Therapy. Manual therapy education in the Netherlands is strongly embedded within international concepts. In these traditional concepts, especially passive joint motion assessment takes a prominent place

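### The 60% specific-agreement gate for strategy B sets no minimum agreement beyond chance, so random decisions are expected to pass it above about 60% prevalence (or below about 40% via p_neg)

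*Protocol article*

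**What the plan says.** The Statistical analysis section treats a lower 95% limit of 0.60 for overall kappa as acceptable reliability. The Discussion carries this forward. If the lower limit exceeds 0.60 and the bias index is below 0.10, patients with a positive indication can be randomised (strategy A, Figure 1A). Otherwise a second route applies: "Should reliability be below this cut-off but with p_pos_ (or p_neg_), arbitrarily, >60%, this strategy can still be used". It randomises only patients on whom two therapists agreed. The Figure 1 legend describes design B as "including only patients positively indicated for SMT by two examiners when kappa <0.60 but p_pos_ (or p_neg_) >60" per cent.

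The two indices "are the proportions of agreement on positive and negative indications, respectively, relative to the total number of positive and negative indications, respectively, from both therapists". In the Discussion they "here indicate the absolute specific agreement on positive or negative indications, respectively, between therapists", so the absence of chance correction is deliberate. The gate has no minimum kappa, no confidence limit and no condition on prevalence.

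The sample size assumes 50% prevalence, but under Potential limitations the authors write that "we cannot rule out the possibility of a substantially higher (or lower) prevalence of positive indications for SMT". The surveys cited there put use of mobilisations between 16% and 83%.

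**The concern.** The same part of the Discussion calls satisfactory reliability a prerequisite for building the decision into a trial, and the Background defines reliability as the ability to discriminate between patients. Strategy B applies when the kappa criterion has failed, so its gate should still show that some discrimination remains. A fixed bar on an index that rises with prevalence cannot do this once prevalence is far enough from 50%.

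If kappa is near zero, a second positive opinion says nothing about the patient beyond the first. The gate could then declare the decision usable when it selects no distinguishable group. The protocol discusses the effect of prevalence on kappa at length, but does not say that p_pos rises with the prevalence of positive decisions and p_neg with that of negative ones.

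Strategy B is not a remote fallback. Under the planning values the expected lower limit of kappa is 0.70 − 0.109 = 0.591, already below 0.60.

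**Working it through.** **Inputs.** From Statistical analysis: N = 165, kappa 0.70, prevalence 50%, half-width 0.109, and the definitions of p_pos and p_neg. From the Discussion and the Figure 1 legend: the 60% gate.

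**The plan's own figure.** The plan states: "With a sample size of 165, a two-sided 95% CI around kappa would extend ±0.109 from the observed value of kappa". With the planning inputs listed above and equal marginals, the large-sample half-width is 1.96 × √((1 − 0.70²)/165) = 1.96 × √(0.51/165) = 0.10897. The stated ±0.109 is reproduced.

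**Expected p_pos and p_neg.** Let p be the prevalence of positive decisions, q = 1 − p, k = kappa, with equal marginals. The cell probabilities are:

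- both positive: a = p² + kpq
- each discordant cell: b = c = pq(1 − k)
- both negative: d = q² + kpq

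Since 2a + b + c = 2p and 2d + b + c = 2q:

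- p_pos = 2a/(2a + b + c) = p + k(1 − p)
- p_neg = 2d/(2d + b + c) = (1 − p) + kp

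At k = 0 these reduce to p and 1 − p. Example with p = 0.70, k = 0, n = 165: the expected cells are 80.85, 34.65, 34.65 and 14.85, so p_pos = 161.7/231 = 0.70. The gate is passed in expectation with no agreement beyond chance.

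**Kappa needed for p_pos = 60%**, that is (0.60 − p)/(1 − p):

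| Prevalence | Kappa needed |
|---|---|
| 30% | 0.43 |
| 40% | 0.33 |
| 50% | 0.20 |
| 55% | 0.11 |
| 60% | 0 |
| 65% | −0.14 |
| 70% | −0.33 |

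The p_neg route mirrors this: the kappa needed falls to 0 at 40% prevalence and is −0.33 at 30%.

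**Chance of passing with random decisions** (k = 0, equal marginals, n = 165, multinomial simulation):

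| Prevalence | p_pos >60% | p_pos or p_neg >60% |
|---|---|---|
| 30% | 0% | more than 99% |
| 40% | 0% | about 50% |
| 50% | 1.3% | about 2.5% |
| 55% | 12% | 12% |
| 60% | about 50% | about 50% |
| 65% | 90% | 90% |
| 70% | more than 99% | more than 99% |

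**Agreement does count at the planned prevalence.** At p = 0.50, p_pos is 50%, 60%, 70% and 80% for kappa 0, 0.2, 0.4 and 0.6. A true kappa of 0.20, the top of the plan's slight band, passes on p_pos about half the time at 50% prevalence and about 98% of the time at 60%.

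**Sensitivity.** Unequal marginals move the threshold a little. Under independence p_pos = 2·p1·p2/(p1 + p2), which gives 58.3% for 50%/70% and 64.6% for 60%/70%. The Discussion does not say whether the gate is read on the pooled table; n = 165 assumes that it is. On one pair's 12 patients, random decisions would pass on p_pos 27% of the time at 50% prevalence and about 75% at 70%.

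**The case against.** The strongest reply is that this is not an analysis rule of the study. The acceptability criterion is the lower limit of overall kappa. The 60% gate sits in the Discussion, is openly called arbitrary, and describes how a later trial could be designed; that trial would need its own protocol. This stands, and it limits the severity. Calling the threshold arbitrary excuses the exact number, however, not a criterion that chance can meet.

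The second reply is that uncorrected indices were chosen on purpose, because skewed prevalence can distort the interpretation of kappa, and that prevalence, the prevalence and bias indices and kappa will be reported alongside. That justifies reporting p_pos and p_neg. It does not justify using them alone to decide, and the gate as written does not call on the other indices.

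A reader might infer that the gate measures prevalence and not agreement. The documents do not support that. Both enter p_pos, and at the planned 50% prevalence random therapists pass on p_pos only about 1% of the time. A reader might also take 83% as the expected prevalence. It is the top of a 16% to 83% range for mobilisation use in surveys; the plan assumes 50%.

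Nor does every failure of the kappa criterion mean kappa near zero. With the stated half-width, an observed kappa of 0.65 has a lower limit near 0.65 − 0.109 = 0.54 and still goes to strategy B. There, two concordant opinions do add information.

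**Conclusion.** The point holds with moderate severity. Above about 60% prevalence of positive decisions, or below about 40% through p_neg, the strategy B gate no longer requires agreement beyond chance. Random decisions pass about half the time at 60% or 40% prevalence and almost always at 70% or 30%. At 50% prevalence the gate works, but its p_pos part asks only for kappa above 0.20.

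The p_neg alternative has a further weakness: it says little about agreement on the positively indicated patients, who are the only ones Figure 1B randomises.

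The figures assume equal marginals, one prevalence shared by all therapists, and a gate read on the pooled 165 patients. Whether prevalence will leave the 40% to 60% range is unknown, but the protocol concedes that it may. It would go too far to infer that the reliability result is compromised: the kappa estimate, its confidence interval and the 0.60 criterion do not depend on this gate. Only the recommendation about a later randomised trial does.

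**What to change.** In the Discussion and the Figure 1B legend, keep p_pos >60% and add a condition on the whole gate that chance can hardly meet, fixed before the prevalence is known. One example is a lower 95% limit of overall kappa above 0.20, the top of the plan's slight band. At n = 165 and prevalence from 50% to 83%, simulation of p_pos >60% with this condition gives about 0% passes at kappa 0, 2% to 3% at kappa 0.20, and 88% to 99% at kappa 0.50.

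Drop the p_neg alternative from this gate, since only patients with two positive indications are randomised, or place it under the same condition. Repairing the p_pos part alone would leave random decisions passing below 40% prevalence. Report p_pos and p_neg beside their chance-expected values, which are the observed prevalences of positive and negative decisions.

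A fixed margin of p_pos over prevalence is not an equivalent substitute. Because p_pos − p = kappa × (1 − p), a margin of 0.10 demands kappa 0.20 at 50% prevalence but 0.50 at 80%.

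The cost is a few words in two places; the confidence interval for overall kappa is already planned. Strategy B will open somewhat less often, and the 0.20 floor is itself a convention that should be stated as such.

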**Figure 1 F1:**
[figure not shown]
**A. Design of an RCT including patients positively indicated for SMT when lower bound of 95% CI around kappa >0.60 and BI <0.10. B**. Design of an RCT including only patients positively indicated for SMT by two examiners when kappa <0.60 but p_pos_ (or p_neg_) >60%.

With respect to our second research objective, it is important to note that empirical evidence for sources of bias and variation in reliability studies is lacking contrary to studies of diagnostic accuracy
[74,93-95]. Variation arises from differences between studies, for example, in terms of demographic and disease features of study participants, characteristics of examiners, setting, or test protocol. As such, it does not lead to biased estimates of reliability, but it can limit the applicability of study results
[94]. Knowledge of factors that explain variation in reliability may inform ways to improve reliability. For instance, examiner training and choosing a group of more heterogeneous study participants have been mentioned as improvement strategies, but both have their limitations and lack supporting evidence
[24]. Systematic reviews may reveal subgroups of participants, examiners, or tests that consistently show higher or lower reliability. In systematic reviews, between-study comparisons are conducted to search for these subgroups as sources of variation. However, these comparisons are less valid as they are hampered by the often strong clinical and methodological heterogeneity between studies
[96]. In addition, the identification of these sources of variation becomes even more troublesome when reliability is consistently low (or high) across studies. Within-study comparisons are the preferred method to explore variation in reliability. To date, very few studies have been undertaken in the field of manual therapy with this aim and method. Cook et al.
[97] investigated factors related to the large variability of forces used during passive accessory intervertebral movements and they found that examiners’ age, gender, experience, background and education, and frequency of use did not contribute to this variation. We present simple logistic regression analysis of concordant decisions as a flexible method that can easily be incorporated in any reliability study to explore and explain variation in reliability from a large number of demographic, professional, and clinical factors.

### Potential limitations of this study

This study protocol presents several new approaches to investigating and analysing decision-making in manual therapy and to reliability research in general. Several of its methods need further discussion in order to appraise their effect on the validity and generalisability of the study’s results. First, establishing examination objectives for physical examination by physiotherapists has been used in earlier studies
[98,99]. However, the prospective formulation and registration of examination objectives is far from common practice for physiotherapists in the Netherlands
[100]. The specific training of our examiners in the formulation and digital registration of these objectives may diminish the generalisability of the estimated reliability of indicating SMT. We encourage that establishing and prospectively registering of examination objectives become an integral part of daily practice in physiotherapy.

Stability of participants’ characteristics is a prerequisite for the valid estimation of reliability
[23]. However, very few empirical data are available as to the minimum length of the time period between test procedures that ensures that patients’ responses to questions and physical tests, such as joint motion assessment, will remain unchanged. Shirley et al.
[101] reported that stiffness responses to repeated mechanical posteroanterior loading of lumbar motion segments returned to the pre-testing state within five minutes. On the other hand, a 30-minute recovery period after 30 minutes of *in vitro* creep loading of the lumbar spine was not sufficient to return to the baseline situation
[102]. By incorporating a 10 minute break for patients between examinations and limiting the number of movement repetitions during PIVM assessment, we are more confident that underestimation of reliability will be avoided. Research into the natural variation over time within and between individuals regarding joint mobility and other body functions, as well as into the variation induced by the physical examination itself, is needed.

Our sample size calculation strongly depends on the assumed prevalence of positive indications which was based on data from the numerous studies on practice patterns among physiotherapists in the treatment of patients with neck and low back pain
[103-113]. Within the large variation in choices of treatment options by therapists, mobilisations and manipulations were only rarely among the most preferred options and their frequency of use ranged from 16% to 83% and from 2% to 37%, respectively. These figures were not substantially different for specific subgroups of manual therapists who reported remarkably low frequencies of use of manipulations in the cervical region
[36,114-116]. As we will consider reliability of indicating either mobilisations or manipulations, or both, we assume a 50% prevalence of positive indications. Choosing a higher or lower prevalence would have resulted in a larger required sample
[117].

In our sample of manual therapists and patients, we cannot rule out the possibility of a substantially higher (or lower) prevalence of positive indications for SMT. Because of such a skewed distribution of decisions, a distorted interpretation of kappa could then occur. Recently, kappa, as a relative measure of reliability, has been criticised because it can only provide information about the ability to distinguish between patients on a sample level
[25]. The authors suggest using the specific agreement parameters (p_pos_ and p_neg_) as absolute measures to quantify observer variation regarding a certain diagnosis or decision on an individual patient level
[25]. No single omnibus index, however, can be satisfactory for all purpose and situations
[69,70]. Therefore, we will calculate all recommended parameters from the 2×2 tables to allow full interpretation of reliability and agreement as related to the prevalence of concordant and discordant indications. We will not, however, correct kappa for prevalence effects and bias, for instance by calculating prevalence-adjusted bias-adjusted kappa, because this would generate values of reliability that no longer relate to the original situation
[117,118].

We will select pairs of manual therapists as examiners that share a common educational background. With this background from the largest institute for manual therapy education in the Netherlands, they likely form a representative sample from the Dutch population of manual therapists registered with the Dutch Association for Manual Therapy or the Royal Dutch Society for Physical Therapy. Manual therapy education in the Netherlands is strongly embedded within international concepts. In these traditional concepts, especially passive joint motion assessment takes a prominent place
[15]. Therefore, we suppose that the results of this study will to a certain extent be generalisable to populations of manual therapists outside the Netherlands. We do, however, suggest that this study be replicated over different countries and concepts to account for local idiosyncrasies in clinical reasoning and decision-making. In addition, for practical reasons, we will choose pairs of manual therapists that work in the same practice. This may inflate reliability and by pairing therapists with different levels of experience, we aim to minimise this potential threat to the validity of the study.

Finally, when analysing the reliability of indicating SMT, we will not distinguish specifically between mobilisations or manipulations. Despite the disparate mechanisms of these interventions
[9,119], no evidence is available on whether one or the other, or both, should be preferred in any clinical situation. Results of randomised controlled trials have been conflicting so far
[120-123]. New research should focus on the relationship between clinical findings, the choice for either mobilisation or manipulation, and subsequent clinical outcomes.

